### Eligibility criteria

Participants must: be aged between 18 and 65; meet *Diagnostic and Statistical Manual of Mental Disorders, Fifth Edition* (DSM-5) criteria for moderate or severe AUD (i.e. at least four symptoms present in the past year); and have used alcohol at least weekly in the month prior to admission to inpatient withdrawal treatment. Patients are excluded from participation if they have a diagnosed history of neurological illness or injury, or any concussion resulting in a loss of consciousness longer than 30 min, or have any diagnosed intellectual disability. Patients assessed by withdrawal unit clinical staff to be unable to safely participate, or without capacity to provide informed consent, due to acute mental or physical impairment (e.g. uncontrolled physical or mental illness or withdrawal-related distress), are not approached for participation. Patients are ineligible to participate if they are currently participating in another clinical trial aiming to test and/or alter outcomes following discharge from inpatient withdrawal, or if they are not planning to stay in the inpatient withdrawal treatment unit long enough to complete four consecutive days of CBM training (See Fig. 1 for the CONSORT participant flowchart).

**Fig. 1 Fig1:**
[figure not shown]
Participant flow through stages of the study

### Measures

#### Demographics

At baseline, a researcher administers a questionnaire assessing participants’ date of birth, identified gender, country of birth, Aboriginal or Torres Strait Islander status, education, relationship status, employment, housing, age of onset of alcohol use, age of onset of alcohol-related problems, number of prior withdrawal treatment episodes, presence of other drugs of concern, presence of substance use disorders among first-degree relatives, psychiatric diagnoses, and (to verify screening) presence of any brain injury or neurological disorders.

#### Alcohol use disorder severity

Alcohol use disorder symptoms are assessed at the baseline interview with the interviewer-administered alcohol use disorder module from the Structured Clinical Interview for DSM-5 Disorders – Research Version (SCID-5 RV), which also verifies eligibility [38]. Severity of physical dependence on alcohol is assessed with the self-administered Severity of Alcohol Dependence Questionnaire (SADQ) [39].

#### Recent alcohol and other substance use

The timeline follow-back (TLFB) interview method is used to quantify number of days of alcohol use and estimated standard drinks consumed [40]. At baseline, the TLFB covers the 30 days preceding admission to the inpatient withdrawal treatment unit. At the 2-week follow-up, the TLFB covers the time since discharge from the withdrawal treatment unit. At the 3-, 6-, and 12-month follow-ups, the TLFB covers the past 30 days. Researchers also use the TLFB to collect information on use of psychoactive medications, including pharmacotherapies for alcohol craving, tobacco and illicit drugs. Because the TLFBs at the 3-, 6-, and 12-month follow-ups do not cover the entire time since the previous follow-up, participants who have not yet lapsed (defined as any alcohol use) or relapsed (defined as 3 days in a row of consecutive alcohol use) at the previous follow-up are asked at the current follow-up whether there was any lapse or relapse since the previous follow-up and, if so, on what date it occurred.

#### Alcohol cravings

Alcohol cravings are assessed using the Alcohol Craving Questionnaire – Short Form – Revised (ACQ-SF-R) [41]. In addition, to monitor participant safety (related to the potential for exposure to alcohol-related imagery to trigger cravings), participants self-rate the intensity of their craving for alcohol immediately before and following each CBM training session, using a single-item visual analogue scale (anchored at the left and right ends with ‘not at all’ and ‘extreme’, respectively). In addition, participants view 20 computerised images (10 of alcoholic beverages and 10 of non-alcoholic beverages) and rate the magnitude of their ‘wanting’ of the pictured beverages by marking a point along an accompanying line with end caps either side indicating ‘I do not want this at all’ to ‘I really want this’. Scores range from 0 to 100, based on the position of the mark (i.e. a mark on the extreme left of the line results in a score of 0 being recorded, while a mark on the extreme right of the line results in a score of 100 being recorded). Within each of the two beverage categories (alcoholic; non-alcoholic), five of the 10 images are identical to images used in the training task (see below) and the other five are novel images not used in other study tasks. This is to allow assessment, following training, of generalisation of reduced cue-evoked wanting from images used in training to other alcohol-related images.

#### Service use

Use of AOD withdrawal treatment services, outpatient AOD counselling, AOD rehabilitation programs, general practitioner services, ambulance call-outs, emergency department visits, and hospital inpatient admissions are assessed with an interviewer-administered, modified version of the Lifetime Drug Use History Questionnaire (LDUH) [42]. At the baseline interview, these questions assess the year prior to the current inpatient withdrawal treatment admission. At each follow-up they assess the time since the previous follow-up (or since discharge in the case of the first follow-up since discharge, i.e. typically the 2-week follow-up), with data from the separate follow-ups then combined for each participant to form a composite assessment of service use over the whole 12-month follow-up period.

#### Approach bias

A modified version of the Alcohol-AAT is used to measure approach bias towards alcohol [24]. Participants are required to react to the format of pictures using a joystick (e.g. push landscape pictures, pull portrait pictures), irrespective of the content of the pictures. There are two categories of pictures (alcoholic beverages; non-alcoholic beverages, 10 unique pictures in each category). The images were selected to represent the beverage type and brands most commonly consumed by this population as documented in the recent pilot study [37]. Each image is repeated twice (for a total of 40 trials) and every picture type appears in landscape and in portrait format 50% of the time. For both categories of pictures (alcoholic; non-alcoholic), the median reaction time (RT) for pull responses is subtracted from the median RT for pull responses to calculate a measure of approach bias.

#### Risk-taking impulsivity

The Balloon Analogue Risk Task (BART) [43] is a validated behavioural measure of risk-taking impulsivity, in which participants are required to inflate a virtual balloon with ‘pumps’, each of which increases a small potential payout. However the balloon may randomly burst at any time, resulting in forfeiture of money earned for that trial. Fifteen trials are administered prior to commencing the first session of CBM. Mean-adjusted pumps (the average number of pumps per banked balloon) will be analysed as a measure of risk-taking impulsivity.

#### Participant assessments of training

After the final training session, participants are asked to rate the training program by reporting, using a five-point Likert-type scale (ranging from ‘strongly agree’ to ‘strongly disagree’), whether or not they believed that the training (i) improved their attention, (ii) reduced their craving for alcohol, and (iii) was interesting. See Fig. 2 for the schedule of measures and training sessions administered.

**Fig. 2 Fig2:**
[figure not shown]
Schedule of measures and interventions. *AAT* approach avoidance task, *ACQ-SF-R* Alcohol Craving Questionnaire – short form – revised, *BART* Balloon Analogue Risk Task, *CBM* cognitive bias modification, *F* follow-up, *S* session, *SADQ* Severity of Alcohol Dependence Questionnaire, *SCID-5* Structured Clinical Interview for DSM-5 Disorders, *TLFB* timeline follow-back

### Interventions

The CBM training is a modified training version of the assessment AAT. Participants are instructed to respond to digitally presented images with a push or pull motion, using a joystick, based on the orientation of the framing of the picture (pushing landscapes; pulling portraits). The training task has been programmed to scale up and down the images in response to pull and push movements, respectively, to simulate the picture expanding towards the participant when ‘pulled’ and receding into the distance when ‘pushed’. As a component of each training session, participants complete a brief practice round involving eight empty frames, to familiarise them with the task requirements. Following the eight practice trials, participants are exposed to presentations of 40 images of alcoholic and 40 images of non-alcoholic beverages, in a random order. Each alcoholic and non-alcoholic beverage is presented three times, for a total of 240 image presentations. Landscape-oriented frames contain alcoholic images in 95% of presentations, implicitly training participants to respond to alcohol with an avoidance movement. The remaining 5% of landscape-oriented presentations contain images of non-alcoholic beverages. Likewise, portrait-oriented images contain non-alcoholic images in 95% of presentations, and alcohol-related images the remaining 5% of the time. During each presentation, the image scales until the joystick reaches its maximal distance. If the response is correct, the next trial then commences after a 500 millisecond inter-stimulus interval (ISI). If the response is incorrect, a large red ‘X’ flashes on the screen and the trial is repeated until the correct response is performed.

The sham training is identical to the CBM training described above, except that each orientation (portrait or landscape) contains alcohol images 50% of the time and non-alcohol images the other 50% of the time. Moreover, instead of instructing participants to respond with approach or avoidance movements, participants are instructed to respond with lateral movements of the joystick, according to picture orientation (left for landscape; right for portrait). As in the experimental training, the image moves, in accordance to the joystick movement, to the left or right edge of the computer screen, at which point the next presentation begins after a 500 millisecond ISI (if the response was correct), or a red ‘X’ flashes and the presentation is repeated (if the response was incorrect). The pictures do not change size in this condition. The sham condition thereby controls for participants’ exposure to alcohol (and non-alcohol) images, and for the demand to attend to image orientation and manipulate the picture with a joystick based on orientation, without including the approach/avoidance component hypothesised to underlie the therapeutic effect of the AAT training.

### Allocation

Site-specific randomisation sequences were generated by a researcher not involved in recruitment or data collection using a random number generator prior to beginning recruitment. A site-stratified 1:1 treatment arm allocation ratio is used, and is based on permuted blocks of variable size. The allocation sequence for each site is programmed into the training task on that site’s task laptop. When opening the training task, the researcher administering the training is prompted to enter the participant’s number, which then automatically causes the program to select the CBM or sham training, based on the pre-programmed randomisation sequence, such that the participant is allocated into a treatment arm ‘automatically’ – with no input from a researcher and without the researcher being able to predict a participant’s allocation prior to randomisation.

### Procedure

Intake AOD clinicians at the participating withdrawal treatment units conduct preliminary screening of patients’ eligibility at admission, and briefly describe the study to patients who appear to meet the eligibility criteria. If patients express interest in participating, the clinician alerts the research team. A member of the research team approaches the patient no sooner than 2 days after their admission and provides them with a comprehensive verbal and written description of the study’s aims and procedures. The research team member obtains written consent if the patient is willing to participate. After the provision of informed consent, but prior to commencing CBM training, a researcher administers the baseline questionnaires to confirm eligibility and assess demographic and clinical characteristics (demographic questionnaire, SCID-5-RV, TLFB), facilitates participants’ self-administration of the ACQ-SF-R, and then proceeds to the computerised assessments (BART, picture wanting ratings, and approach bias measurement). To avoid participant fatigue, service use and SADQ questionnaires are occasionally delayed to the second or third day of training, but may also be administered on the first day if the participant prefers.

After they have completed the pre-training measures, participants are randomised into a treatment arm by the computer and begin their first training session. Training sessions continue on each of the next 3 days (i.e. 4 consecutive days of training in total). Following the final training session, participants repeat picture wanting ratings, the approach bias measurement task, ACQ-SF-R, and the three-item task rating. After their discharge from the withdrawal treatment unit, a researcher records the types, frequency, and dosages of any medications administered to participants during their admission, and makes copies of any relevant clinical notes taken at admission. Another researcher not involved with the participant’s training administration – and therefore blinded to their treatment allocation – contacts them at 2 weeks, 3, 6, and 12 months post-discharge to conduct telephone follow-up interviews consisting of the TLFB, service use questions, and ACQ-SF-R. Following intention-to-treat principles, participants who unexpectedly discharge from the inpatient withdrawal treatment unit prior to completing all four sessions of training are still contacted for follow-up, unless they withdraw from the research. Participants may withdraw at any time, and if they do, no further training or questionnaire measures are conducted. Participants are informed, prior to providing their consent to participate, that if they withdraw, their data collected prior to their withdrawal treatment will be retained for inclusion in analyses unless they explicitly rescind permission to retain these data.

### Outcome measures

The primary outcome of interest to this study is the difference between treatment arms in proportion of participants reporting abstinence from alcohol 2 weeks after discharge, measured with the TLFB. Secondary outcomes of interest are abstinence at the subsequent follow-ups (measured with the TLFB), the difference between treatment arms in healthcare costs incurred due to acute/emergency healthcare treatment and readmission to AOD withdrawal treatment during the follow-up period (service use measured with the LDUH, with costs of treatment episodes to be estimated with the assistance of a health economist), and differences in cue-evoked desire for images of alcohol after the final session of CBM training. Secondary analysis will also examine the degree to which baseline approach bias towards alcohol moderates the effectiveness of CBM training on the primary outcome. Additional exploratory analyses are planned to investigate (i) moderating effects of pre-admission history of withdrawal treatment, severity of alcohol dependence and cravings, and impulsivity on the primary and secondary outcomes; (ii) whether alcohol cravings (as measured by the ACQ-SF-R) are affected by CBM; and (iii) whether CBM affects time to relapse.

### Data management

Prior to analyses, data cleaning and verification will be conducted for all data entered manually (i.e. data collected using paper questionnaires). Range checks will be conducted on all fields to detect outliers and incorrect entries. Entries subsequently confirmed to be incorrect, after checking paper records, will be amended. Following this, a random sample of 10% of the cases from key fields will be re-entered. Where this results in discrepancies between the original data and the re-entered data, we will determine whether the original data was erroneous, and correct it if so. Using this method, any field that has a higher than 2% error rate will be completely re-entered.

### Statistical methods

The main analyses of the primary and key secondary outcome variables will follow the intention to treat (ITT) principle and will include all randomised patients regardless of completion of the training phase or loss to follow-up (the full analysis set). A supportive analysis of the primary outcome will be restricted to participants who completed all four training sessions and were subsequently assessed 2 weeks after discharge (the per protocol set).

### Primary outcome

In the ITT analysis of the primary outcome, the divisor for the proportion of abstinent participants in an arm will be the number randomized to that arm and individuals for whom alcohol use during the first 14 days post-discharge was not assessed, for any reason, will be deemed not to be abstinent. These proportions will be compared using a two-sample binomial test (two-sided α = 0.05) and a 95% confidence interval for the difference in the proportions will also be reported. The Cochran-Mantel-Haenszel test, stratified by site, will be conducted as a supportive analysis. In a further supportive analysis of the primary outcome, participants who complete fewer than four training sessions or who miss the 2-week assessment, will be excluded from the denominator (and the numerator) when the proportion of abstinent patients is calculated in each arm. This ‘per protocol’ analysis will use the same statistical methods as the ITT analysis.

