### Sample size

Our recent pilot study indicated a difference in abstinence rates of 22% (i.e. 69% vs 47%) between the CBM and sham training groups. Using a smaller conjectured difference of 20% (e.g. 65% vs 45%) a two-sample, binomial test (two-sided α = 0.05) that utilises a pooled estimate of the variance, has 90% power to detect the conjectured difference when a total of 256 participants is randomised (i.e. 128 in each treatment arm). With an allowance for up to 15% drop out in the 2 weeks after discharge, based on an observed retention rate of 86% at 2 weeks in the pilot study, the target sample size was set at 300 (i.e. 150 randomised to each treatment arm). Recruitment is expected to take 22 months, given the throughput in the withdrawal treatment units, and the total study duration is likely to be 36 months.

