### Key secondary outcome and moderation analysis

Assessments of abstinence in the 30 days prior to each of the 3-, 6- and 12-month follow-ups will also be analysed in the same way as the ITT analysis of the primary (2-week) endpoint – participants not assessed for any reason will be deemed to have relapsed. In a supplementary analysis of all available follow-up assessments (from 3 to 12 months), that assumes any missing follow-ups are missing completely at random, a logistic regression analysis, using the method of generalized estimating equations (GEE), will be used to compare the arms, and changes over time in the arms, adjusting, if need be, for sites. An additional supplementary, missing not at random (MNAR), analysis will use a Bayesian approach, and Markov chain Monte Carlo (MCMC) to jointly model abstinence and missingness. The model will include a random effect for each participant and minimally informative, normal prior distributions for parameters in the logistic models for abstinence and missingness. Parameter estimates and their associated 95% credible intervals, based on posterior distributions, will be reported. The MNAR approach will also be used to investigate the moderating effect of the baseline approach bias score. Additional exploratory analyses, also using the MNAR approach, will investigate adjusting the estimated difference between the arms for such covariates as age, gender, and SADQ score. Full details will be given in the statistical analysis plan (SAP) that will be documented prior to the analysis of the primary outcome.

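### Randomisation is stratified by site but the primary test and its confidence interval are not; if abstinence differs between sites, both are mildly conservative, and correcting this costs nothing

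*Protocol article*

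**What the plan says.** Allocation section: "A site-stratified 1:1 treatment arm allocation ratio is used, and is based on permuted blocks of variable size". Study setting gives three withdrawal units, so there are three strata.

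Primary outcome section, on the ITT proportions: "These proportions will be compared using a two-sample binomial test (two-sided α = 0.05"), together with a 95% confidence interval for their difference. Neither has a site term. Site enters in the next sentence: "The Cochran-Mantel-Haenszel test, stratified by site, will be conducted as a supportive analysis". The per-protocol analysis uses the same methods as the ITT analysis.

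Key secondary outcome section: abstinence at 3, 6 and 12 months is tested in the same way as the primary ITT comparison. A supplementary GEE model compares the arms "and changes over time in the arms, adjusting, if need be, for sites".

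Sample size section: the calculation uses the same unstratified test, one "that utilises a pooled estimate of the variance", with 65% against 45% abstinence, and finds that it "has 90% power to detect the conjectured difference when a total of 256 participants is randomised (i.e. 128 in each treatment arm").

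**The concern.** Blocking 1:1 within site forces the arms to have nearly the same site mix. Differences in abstinence between sites therefore largely cancel from the difference between arms, and the true sampling variance of that difference contains only within-site variation. The pooled binomial variance is computed as if all participants came from one population, so it still includes the between-site part. If sites differ, the estimated standard error exceeds the true one, the p-value is too large on average and the 95% interval too wide.

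What is at stake is the calibration of the headline test and interval. The supportive CMH test covers the p-value but not the interval, because no site-stratified risk difference or interval is stated.

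**Working it through.** **1. The plan's own figure.** Inputs from the Sample size section: 65% and 45%, mean 0.55, two-sided 5%, 90% power, pooled variance under the null.

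n per arm = [1.96·√(2·0.55·0.45) + 1.2816·√(0.65·0.35 + 0.45·0.55)]² / 0.20² = [1.379 + 0.883]² / 0.04 = 127.9, so 128.

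Power at 128 per arm is 90.0%. The stated 256 in total reproduces for the unstratified test.

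**2. How far the unstratified variance is too large.** The article gives no site-specific abstinence rates. Assume three equal sites with mean 0.55 (the midpoint of 65% and 45%) and three spreads. The ratio r is the mean within-site p(1−p) divided by the pooled p(1−p) = 0.55·0.45 = 0.2475.

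- 45/55/65%: (0.2475 + 0.2475 + 0.2275)/3 = 0.2408; r = 0.973
- 40/55/70%: (0.2400 + 0.2475 + 0.2100)/3 = 0.2325; r = 0.939
- 35/55/75%: (0.2275 + 0.2475 + 0.1875)/3 = 0.2208; r = 0.892

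The crude standard error is too large by a factor 1/√r: about 1.4%, 3.2% and 5.9%.

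**3. True size of the nominal 5% test.** Size = 2·P(Z > 1.96/√r): 4.7%, 4.3% and 3.8%.

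**4. Power.** A nominal 90% design has a mean test statistic of 1.96 + 1.2816 = 3.2416. When sites differ, the crude statistic keeps that mean but has standard deviation √r, so its power is Φ(1.2816/√r). The stratified statistic has mean 3.2416/√r and standard deviation 1, so its power is Φ(3.2416/√r − 1.96). The equivalent increase in sample size, k, is the factor at which the crude test reaches the stratified test's power: (3.2416·√k − 1.96)/√r = 3.2416/√r − 1.96.

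| Assumed site rates | Crude power | Stratified power | Gain (points) | Sample-size equivalent |
|---|---|---|---|---|
| 45/55/65% | 90.3% | 90.8% | 0.5 | under 2% |
| 40/55/70% | 90.7% | 91.7% | 1.0 | about 4% |
| 35/55/75% | 91.3% | 92.9% | 1.6 | about 7% |

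A simulation of the last row with 43 per site per arm gave 91.8% against 93.4%.

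**5. Cross-check by simulation.** 200,000 trials per scenario, three equal sites, exact balance within site, a common odds ratio, marginal rates held at 65% and 45%, 128 per arm:

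| Sham abstinence by site | Crude power | CMH power | Crude size | CMH size |
|---|---|---|---|---|
| 45/45/45% | 90.2% | 90.2% | 5.1% | 5.1% |
| 35/45/55% | 90.6% | 90.7% | 4.8% | 4.9% |
| 31/45/60% | 90.8% | 91.3% | 4.6% | 5.0% |
| 26/44/64% | 91.3% | 92.6% | 4.1% | 5.1% |
| 19/44/72% | 92.4% | 94.8% | 3.0% | 5.0% |

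The size columns come from runs with both arms at the sham rates. At 150 per arm the gains are smaller: about 0.4 points for the 26/44/64% pattern and 1.1 for the most extreme one.

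**The case against.** The best defence is that the plan is prespecified, internally consistent and errs on the safe side. The trial is sized on the same unstratified test that it uses, the 90% power reproduces, the site-stratified test is already planned, and all three units are in one metropolitan area, so site differences may be small. All of that stands, and it limits the point to a minor one. It leaves the primary interval without a site-stratified counterpart, and it gives no reason to rank the test that ignores the randomisation strata above the one that respects them.

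A reader might go further in several ways that the article does not support.

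- *Power is certainly being lost.* The loss depends on sites differing, and no site rates are given. Without site differences there is essentially none.
- *The test is invalid or the trial underpowered because site is ignored.* The error is conservative, and crude power stayed at 90% or above in every scenario at 128 per arm.
- *A 10.8% lower variance at 35/55/75% is worth about 12% more participants (1/0.892 = 1.12).* Blocking has already lowered the true variance of the crude difference, so the crude test gains power too. Stratifying corrects the estimated standard error, and the equivalent is about 7%.
- *Two tests leave two answers to one question.* The Primary outcome section ranks them: the binomial test decides and CMH supports.
- *The conditional site adjustment in the GEE is a data-driven choice.* That wording concerns a supplementary analysis, does not say that outcome data will decide, and sits in a section that defers full details to a SAP not shown here.

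**Conclusion.** The mismatch between design and primary analysis is real and fixed in the text. Its consequence is conditional and small. If sites differ in abstinence by 20 to 40 points from lowest to highest, the nominal 5% test runs at about 4.7% to 3.8%, and stratifying adds about 0.5 to 1.6 points of power. Only a wider spread, such as 19% to 72% in the sham arm, brings the gain to about 2.5 points at 128 per arm. The site rates, equal site sizes and common odds ratio are assumptions. The direction does not depend on the particular rates chosen: with 1:1 blocking within site, ignoring site makes the test and interval conservative and does not inflate type I error. This is a free improvement of minor weight, and no threat to the trial's validity or its stated power.

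**What to change.** In the SAP, before unblinding:

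- make the site-stratified CMH test the primary test;
- report the Mantel-Haenszel risk difference over the three sites with its 95% confidence interval as the primary estimate;
- keep the unstratified binomial test and crude interval as supportive;
- apply the same rule to the 3-, 6- and 12-month ITT tests and to the per-protocol analysis.

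Including site in the GEE as a fixed design factor would be consistent with this.

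The cost is an exchange of labels between two tests already planned, plus one added estimate with its interval. It needs no new data and no change to the sample size. The change and its date should be recorded, since the article names the unstratified test as the main analysis.
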